### Study design and setting

The study is a cluster randomized controlled evaluation of a group-based peer support program, implemented and reported in accordance with the requirements of the CONSORT statement [17] and its extension to cluster randomized trials [18]. The study is being conducted in Victoria, Australia, a state that is divided into 79 local government areas (LGAs) within five regional and three metropolitan health regions. Community (defined as a post code area) peer support groups consisting of 10 – 12 participants are recruited, undergo baseline assessment, and then all participants are offered the opportunity to attend a one day diabetes self-management education (DSME) program to ensure that the intervention group does not simply use the sessions to obtain diabetes education rather than peer support. Finally, the groups are randomized to either an intervention arm or usual care arm with group postcode location being the unit of randomization. Groups assigned to the intervention arm participate in the peer support program for 12 months, while those assigned to the control arm continue with their usual care. Figure 1 is a CONSORT diagram of the study design. 

**Figure 1 F1:**
[figure not shown]
**Australasian Peers for Progress – Consort Diagram for Diabetes Project Study Design**.

### Ethics approval

The study received ethics approval from the Monash University Human Research Ethics Committee (MUHREC) Project number CF09/1692 – 2009000920. Participants were given a detailed participant information sheet after which signed informed consent from all participants is obtained.

### Eligibility criteria

Participants and peer leaders, able to understand English, aged between 25 – 75 years and diagnosed with T2DM for more than 12 months are eligible. Participants are excluded if they have a current debilitating medical or related condition (e.g. severe mental illness or end-stage cancer).

Self-identified peer supporters are interviewed by the project staff using a set script to assess their current diabetes management regimen, their attitude with respect to the involvement of a clinical care team in diabetes management, their compassion and understanding of difficulties people with diabetes may encounter and their attitude towards referral and seeking assistance when required. Previous life experience, especially working with groups or as community leaders and language abilities is considered favourably.

### Sample size calculations

Sample size was determined by a requirement to have sufficient power to detect a meaningful difference between intervention and control group means of participant UKPDS score changes from baseline to 12 months. During the study, both groups will age by 1 year, which will increase their UKPDS risk calculation by identical amounts [16]. We anticipate this increase would be offset by reductions due to improvements in systolic blood pressure, total cholesterol/HDL cholesterol ratio, HbA_1_C, or smoking status. Assuming a standard deviation of 5% in baseline to 12 month UKPDS changes in both groups, 100 individuals per study arm with 12 month follow-up are required to provide 80% power to detect, with a 2 sided p-value of 0.05 for significance, a mean reduction of cardiovascular risk in the peer support arm that is 2% greater than any mean reduction in the usual care arm. The clustering of individuals by actual peer group (intervention arm) or future group (usual care arm) was not adjusted for because the comparisons across clusters are within-person changes over time and previous studies of UKPDS change in similar clusters found no clustering effects. Hence 12 groups and 120 participants per arm are required at baseline.

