### Recruitment

DA–Vic administers the National Diabetes Services Scheme (NDSS), an initiative of the Australian Government, which contains contact details for more than 85% of all clinically confirmed cases of diabetes (including type 1, type 2 and gestational) in Victoria. Benefits of NDSS registration include access to diabetes related products at subsidized prices [19]. DA–Vic facilitated contact with people diagnosed with T2DM in Victoria and registered on the NDSS database. Diabetes prevalence data from each of the 79 local government areas (LGAs) in Victoria [20] identified 10 regional towns, two from each non-metropolitan Melbourne health region, and 12 metropolitan post codes in the three metropolitan health regions for recruitment. Locations are suitable if the population was more than 10,000 and the density of NDSS registrants was more than 2.5%. Figure 2 shows group location by health region. 

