**Figure 2 F2:**
[figure not shown]
**Australasian Peers for Progress Diabetes Project Group locations in Victorian Health regions****.** Two locations were selected for randomisation in four of the five rural health regions. The regional centre of Geelong in the rural health region of Barwon South Western and each of the three metropolitan health regions had sufficient population and area to support the selection and randomisation of four group locations. An additional group was initiated as a pilot group in the western Metropolitan health region.

Prospective participants, enrolled on the NDSS database for more than 1 year, who indicated willingness to be contacted for research purposes, are resident within the selected location, and are aged between 25 – 75 years are invited by mail to contact the project team if interested in receiving further information about participating in the study as a peer supporter or as a group member. General Practitioners (GPs), community health centres, pharmacies, diabetes clinics, podiatrists, optometrists and any active DA–Vic ComNet groups or other community based groups within the selected locations are also targeted with posters and brochures to increase study exposure.

Self-identified peer supporters and participants with an interest in the project are sent comprehensive explanatory statements, outlining the aims of the study and the randomisation process. Participants are asked to return a signed informed consent indicating their agreement to participate whilst acknowledging their ability to withdraw if desired.

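### The 80% power figure sets the design effect to 1 in a group-randomised trial; the within-person-change argument does not justify that, and the empirical argument is unquantified

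*Protocol article*

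**What the plan says.** All of the sample size inputs are in the protocol article, Sample size calculations:

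- Variability: "Assuming a standard deviation of 5% in baseline to 12 month UKPDS changes in both groups".
- Target difference: "a mean reduction of cardiovascular risk in the peer support arm that is 2% greater than any mean reduction in the usual care arm".
- Test and size: "100 individuals per study arm with 12 month follow-up are required to provide 80% power to detect" this difference, "with a 2 sided p-value of 0.05 for significance".
- Clustering by peer group (actual or future) "was not adjusted for because the comparisons across clusters are within-person changes over time". The same sentence gives a second reason, that earlier studies of change in UKPDS risk in comparable clusters showed no clustering. No ICC, interval or reference accompanies it.
- Enrolment: "Hence 12 groups and 120 participants per arm are required at baseline".

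Study design and setting makes the group's postcode location the unit of randomisation. Intervention condition describes monthly meetings led by a trained peer supporter, with content that varies by group. Data analysis names an analysis of covariance: 12-month value regressed on baseline value and arm.

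On the number of locations, Recruitment lists "10 regional towns, two from each non-metropolitan Melbourne health region, and 12 metropolitan post codes". The Figure 2 legend says "Two locations were selected for randomisation in four of the five rural health regions", with four in the fifth rural region (Geelong) and four in each of the three metropolitan regions.

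**The concern.** In a cluster trial, the variance of the arm comparison is inflated by the correlation, within groups, of whatever outcome is compared. Here that outcome is change in UKPDS risk. Subtracting baseline removes whatever is constant for a person or community. It leaves untouched any tendency of people in the same group to change together. A shared supporter, shared meetings and a shared locality are direct reasons to expect some such tendency, at least in the intervention arm. The first reason therefore does not support a design effect of 1.

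The second reason is about clustering of change, which is the right quantity. As written, though, it could mean only that no clustering was detected. It does not establish an ICC of exactly zero, which is what the calculation needs.

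At stake is how the primary result will be read. If the trial finds no difference, it will be judged against a claimed 80% power to detect 2 points, and that power has been shown only for the independent case.

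**Working it through.** **Inputs from Sample size calculations.** SD of change 5, difference 2, two-sided 0.05, power 80%, 100 completers per arm, 12 groups per arm, 120 per arm at baseline. Completers per group: m = 100/12 = 8.33. Implied loss: 1 − 100/120 = 16.7%.

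**Inputs not in the document (assumptions).** The ICC of change, taken as 0.01, 0.02 and 0.05, and the correlation between baseline and 12-month values, taken as 0.6 to 0.8.

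**Step 1. Reproduce the stated size.** n = 2 × (1.96 + 0.842)² × 5² / 2² = 98.1, so 99 per arm against 100 stated. Power at 100 per arm is 80.7% by normal approximation and 80.4% by t test on 198 df. Inflation: 100/(1 − 1/6) = 120. The arithmetic is right for independent observations.

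**Step 2. Allow for clustering of change.** Design effect DE = 1 + (m − 1) × ICC. Standard error of the difference = 5 × √(2 × DE/100). Power is given by normal approximation and by the noncentral t on 24 − 2 = 22 df.

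| Assumed ICC | DE | SE | Power, normal | Power, 22 df |
|---|---|---|---|---|
| 0 | 1.00 | 0.707 | 80.7% | 77.1% |
| 0.01 | 1.07 | 0.733 | 77.9% | 74.2% |
| 0.02 | 1.15 | 0.757 | 75.2% | 71.4% |
| 0.05 | 1.37 | 0.827 | 67.7% | 63.8% |

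By normal approximation, power drops below 80% once the ICC exceeds about 0.003. The 22 df column costs a further 3 to 4 points, and that cost is present even at ICC 0.

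**Step 3. Detectable difference.** On the change-score basis with 22 df, 80% power corresponds to a difference of about 2.15 points at ICC 0.01, 2.22 at 0.02 and 2.42 at 0.05.

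**Step 4. Credit the planned analysis of covariance.** With equal variances at the two times and correlation ρ, its residual variance is (1 + ρ)/2 times the change-score variance: 0.90 at ρ = 0.8, 0.85 at 0.7 and 0.80 at 0.6. The same DE is applied. Power on 22 df:

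| Assumed ICC | ρ = 0.8 | ρ = 0.7 | ρ = 0.6 |
|---|---|---|---|
| 0.01 | 79% | 81% | 83% |
| 0.02 | 76% | 78% | 81% |
| 0.05 | 68% | 71% | 73% |

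**Step 5. Count the locations.**

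- Recruitment: 5 × 2 + 12 = 22.
- Figure 2 legend: 4 × 2 + 4 + 3 × 4 = 24, with a pilot group mentioned separately.
- Sample size calculations: 2 × 12 = 24.

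The difference of two lies in the Geelong region, which has two locations in Recruitment and four in the legend.

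**The case against.** The strongest defence is that the sums are correct on the stated assumption and that the assumption has an empirical basis. That basis concerns change in UKPDS risk, not its level. A condensed article may leave out the references, and a reader who cannot see the earlier studies cannot call the statement false. This stands. It rules out the tempting inference that the trial simply lacks its stated power: the shortfall depends on an ICC that the document does not give, and every non-zero ICC used here is an assumption.

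A second defence is that the 22 df figures and the change-score basis are both unfavourable. Data analysis names no cluster-level test, and its analysis of covariance is more efficient than change scores. This also stands in part. At ICC 0.01 to 0.02 and correlations of 0.6 to 0.7, power is about 78 to 83%, so the loss can be fully offset. At ICC 0.05 it is not. The plan, however, derives its size from change scores and states no correlation.

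A third is that more data may be available. If all 120 per arm were followed (m = 10), power on 22 df would be 81% at ICC 0.01, 78% at 0.02 and 69% at 0.05. The plan counts on only 100.

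Two further inferences are not supported:

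- The planned regression on group-level characteristics asks whether such variation exists. It does not concede that it does.
- The 22 locations in Recruitment do not show that the trial has only 22 clusters. The legend explains the four Geelong locations and agrees with the 24 groups required, so a separate power figure for 22 groups is not warranted.

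**Conclusion.** The concern holds as a fault in an assumption, not in arithmetic. The within-person argument does not justify ignoring clustering, and the empirical argument is unquantified. On the plan's change-score basis, 80% power holds only if the ICC of change is essentially zero and individual-level degrees of freedom are used. Over an assumed ICC of 0.01 to 0.05, with 8.33 completers in each of 12 groups per arm, change-score power is about 78% down to 68% by normal approximation, or 74% down to 64% on 22 df. Analysis of covariance moves the latter range to about 79% down to 68% at an assumed correlation of 0.8, and to about 83% down to 73% at 0.6. The mismatch in location counts is secondary and needs only to be reconciled.

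**What to change.** In Sample size calculations:

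1. Delete the within-person-change justification.
2. State the ICC of change from the earlier studies, with its source and uncertainty.
3. Restate power for 24 groups, using 1 + (m − 1) × ICC and cluster degrees of freedom over an assumed ICC range of 0.01 to 0.05. Give it with and without the gain from analysis of covariance, and state the correlation assumed. Alternatively, keep 80% and state the larger detectable difference, about 2.15 to 2.4 points for change scores on 22 df.

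In Recruitment, reconcile the location count with the 24 groups, for example by noting the four locations in the Geelong region.

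The cost is text only. No extra enrolment is needed, but the stated power is likely to be less favourable.

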### Recruitment

DA–Vic administers the National Diabetes Services Scheme (NDSS), an initiative of the Australian Government, which contains contact details for more than 85% of all clinically confirmed cases of diabetes (including type 1, type 2 and gestational) in Victoria. Benefits of NDSS registration include access to diabetes related products at subsidized prices [19]. DA–Vic facilitated contact with people diagnosed with T2DM in Victoria and registered on the NDSS database. Diabetes prevalence data from each of the 79 local government areas (LGAs) in Victoria [20] identified 10 regional towns, two from each non-metropolitan Melbourne health region, and 12 metropolitan post codes in the three metropolitan health regions for recruitment. Locations are suitable if the population was more than 10,000 and the density of NDSS registrants was more than 2.5%. Figure 2 shows group location by health region. 

**Figure 2 F2:**
[figure not shown]
**Australasian Peers for Progress Diabetes Project Group locations in Victorian Health regions****.** Two locations were selected for randomisation in four of the five rural health regions. The regional centre of Geelong in the rural health region of Barwon South Western and each of the three metropolitan health regions had sufficient population and area to support the selection and randomisation of four group locations. An additional group was initiated as a pilot group in the western Metropolitan health region.

Prospective participants, enrolled on the NDSS database for more than 1 year, who indicated willingness to be contacted for research purposes, are resident within the selected location, and are aged between 25 – 75 years are invited by mail to contact the project team if interested in receiving further information about participating in the study as a peer supporter or as a group member. General Practitioners (GPs), community health centres, pharmacies, diabetes clinics, podiatrists, optometrists and any active DA–Vic ComNet groups or other community based groups within the selected locations are also targeted with posters and brochures to increase study exposure.

Self-identified peer supporters and participants with an interest in the project are sent comprehensive explanatory statements, outlining the aims of the study and the randomisation process. Participants are asked to return a signed informed consent indicating their agreement to participate whilst acknowledging their ability to withdraw if desired.

### Diabetes self-management education

All enrolled participants (including identified peer supporters) are invited to attend one day of diabetes self-management education (DSME), held in ten locations around the state of Victoria. Education is delivered by a credentialed diabetes educator and accredited practising dietician from DA–Vic. The seven-hour program covers basic disease information, good self-management practice including diet and physical activity, disease complications and medications. A project specific education manual is given to each attending participant. Participants who cannot attend a full day program are sent the education manual and a copy of a DVD, filmed during one of the program education sessions and supplemented with visual material to reiterate DSME messages.

### Allocation

Upon completion of recruitment (participant and peer supporter), DSME and baseline measurement, groups are randomized in each health region (comprising 2 or 4 groups) so that each health region contained an equal number of intervention and usual care groups. Allocation to intervention or usual care was governed by a random number generation process using Stata statistical software, Release 11.

### Usual care

Participants and supporters from locations allocated to the control arm continue to receive their usual care and receive a copy of all anthropometric and biomedical measurements collected at baseline, 6 & 12 months with a recommendation to share these results with their clinical team.

### Intervention condition

Figure 3 summarizes the different components of the peer support intervention program. This multi faceted intervention comprises four interconnected components to deliver support to the participants.

Monthly local community based meetings, facilitated by a trained peer supporter.

Regular contact between supporters and participants, in person or by phone, to offer support and assistance.

A manual and resource book, developed specifically for this program.

Access to a password protected website containing further information, resources and education vignettes.

**Figure 3 F3:**
[figure not shown]
**Australasian Peers for Progress Diabetes Project Intervention components and outcomes**.

Participants are encouraged and reminded by the supporter to attend all of the scheduled monthly group sessions during which the group members discuss and share challenges of diabetes management and support each other to set and achieve goals. Apart from meetings one and twelve, the content of the group meeting is flexible and is determined by the particular concerns and characteristics of individual groups. Suggested topics for discussion include risk assessment, goal setting, linkage to clinical care, diet, exercise, feet care, optical and mental health. The group members, according to their needs and interests, arrange visits to the group meetings by local health care professionals.

Providing support to each other through regular supporter-participant or participant-participant contact, between monthly sessions is promoted in order to maintain motivation and encourage self-improvement and confidence in diabetes self management. Participants and supporters are encouraged to meet socially, for shared activities (walks, exercise classes) and to motivate and encourage each other beyond the time spent together at the monthly meetings.

Participants receive a manual/workbook, to use during and outside the monthly meetings, which provides educational information including health recommendations and guidelines for diabetes management, helpful tips and advice for managing diabetes, information about available clinical care and tips on how to facilitate access to and use clinical care effectively. This manual also has space for recording goals, challenges, clinical measures and notes from discussion arising during the meetings.

Participants have access to a password protected website which offers additional resources to support group meeting discussions and activities. It provides links to other health and diabetes-related websites so that participants can easily navigate to relevant pages if they are looking for specific information regarding their diabetes management. It also contains recorded vignettes of the education session delivered to all participants prior to randomisation.

A bi-monthly newsletter “Support Share Learn Live” containing project news, support group profiles and photos, healthy recipes, and information to supplement meeting topics is posted to all intervention participants.

Supporters are asked to maintain and record; using a monthly contact record sheet, email or phone contact with group members throughout the month at which time they may inform participants about upcoming meetings or group activities as well as provide additional support. The monthly contact record also requires supporters to provide details of discussions and topics covered at each meeting.

### Peer supporter training & support

Suitable peer supporters from locations randomized to the intervention arm are trained over two and a half days by a credentialed diabetes nurse educator experienced in group facilitation training. Peer supporter training aims to equip supporters with communication and group facilitation skills to help them support their group members to tell their stories, set goals, problem solve, increase awareness and linkages with the available health system, optimize self-management behaviours, including glucose monitoring, dietary changes and physical activity, as well as provide emotional support. The work with the research team with respect to data collection including reports of group meetings and individual contacts is reviewed and explained during the training. Additionally, peer supporters are invited to assist with scheduling meetings and to locate potential venues for group meetings within their communities.

Peer supporters are supported during the intervention period through weekly teleconferences with the project and specialist staff including diabetes educators, dieticians and psychologists. Furthermore, peer supporters receive a weekly informational e- newsletter about aspects of diabetes care and self-management, additional information in response to questions from group members and information they might share with their group members as well as reminders about joining the teleconference the following week and minutes from the preceding teleconference (Figure 3). Peer supporters are asked to attend at least one teleconference each month. These calls, which are recorded, emulate a supportive peer group meeting in that discussion and conversation with the project staff will provide organisational and informational support and the supporters provide experiential, emotional and social support to each other. During these teleconferences, supporters review their group meetings, discuss important events, share stories, ask questions on behalf of their group members and receive support from their peers.

